#### Statistical analysis

Results will be reported according to CONSORT guidelines for cluster randomized trials. A purposely built survey has been developed. Surveys will be checked for completeness prior to being scanned and sent for processing with a data management service. Pathology data will be extracted by the study pathology provider. Data will be uploaded into Stata 12 for further cleaning and analysis.

Descriptive statistics will be used to summarize GP, PN, and participant factors for the two study groups and to check for any imbalance in potential confounders. The individual participant will be the unit of analysis and the analytical methods will allow for clustering of individuals within the practice. Marginal logistic model using generalized estimating equations with robust standard errors will be used to compare binary outcomes between the two study arms. Mixed-effects linear regression will be used to compare the means between study arms for continuous outcomes, adjusting for baseline outcome measure. Stratification variables will be included as fixed effects. Analysis will be conducted on an intention to treat basis, with any imbalance of confounders between study groups adjusted for in the regression analysis.

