### Recruitment and randomization of practices

Eligible general practices must have a current PN. Practices are recruited using our University Department of General Practice database (the VicREN practice based Research Network) and through Medicare Locals. Practice randomization is stratified by practice size, location in Community Health Centers, and participation in the National Primary Care Collaboratives.

The unit of randomization is the practice. Practices are randomized after consenting, and following recruitment of at least one eligible patient (Additional file 1). Due to the nature of the intervention and because further patient recruitment often occurs over a period of months subsequent to randomization, full allocation concealment is not possible. Randomization is in blocks, undertaken by a statistician at the University of Melbourne independent of the research team. Following randomization, the research team assist practices to continue to identify and recruit patients.

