### Participant identification and recruitment

Patient identification is conducted by practices employing a number of methods to generate a comprehensive list of potentially eligible patients. Search methods vary by practice but include searching the practice electronic medical records database, using the Pen clinical audit tool [30], or obtaining a list of HbA1c results from the local pathology providers. Our previous research and pilot suggests an average general practice (of two full-time GPs) has 80 to 100 identified patients with T2D, 10% to 15% (8 to 15) of whom meet inclusion criteria.

Recruitment involves a letter from the practice inviting eligible patients to participate and a follow-up call from the PN and/or GP. The invitation letter states that participants may benefit from assessment and more intensive treatment of their diabetes and that insulin may be a part of that program. Patients are invited to express interest in receiving further details about the study, to attend the practice to learn more about the study from a member of the study team. If the patient agrees to participate, consent and baseline data are collected at that visit. Patients are asked to have their HbA1c checked and are subsequently excluded if the result is <7.5%.

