### Data collection and outcomes measures

#### Outcomes

The primary outcome is change in HbA1c (measured as a continuous variable). Secondary outcome measures include the number of participants who successfully transfer to insulin and the proportion of participants who achieve HbA1c measurement of <7.0%. We will also collect data on other outcome measures of interest including the proportion of participants who achieve individualized HbA1c targets according to Australian Diabetes Society guidelines, changes in psychometric scores including AQoL-8D, PHQ-9 and PAID and net healthcare utilization and costs. Research assistant (RA) staff will collect participant data at baseline and at 12 months using the instruments and measures outlined in Table 1. HbA1c is also collected at six months.

**Table 1 T1:** Outcome measures and collection time points

**Measure**	**Baseline**	**6 months**	**12 months**

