### Analysis

#### Power calculation and sample size

Our sample size calculation is based on the primary outcome. A total of 224 participants (average of three participants per practice) from 74 general practices are required to detect an absolute 0.5% mean HbA1c difference over 12 months between control and intervention groups with 80% power and a standard deviation (SD) of 1 using two-sided alpha of 0.05. Sample size calculation allows for a design effect of 1.05 and is based on a conservative estimate of the intra-cluster correlation (ICC) for HbA1c of 0.05 [44] and attrition rate of 10% for practices and participants.

In a community observational study [23], over a five-year period, about 2% of the community sample changed from oral treatment to insulin per year. We conservatively assume a background rate 10 times this or 20% per year in the control group. Based on our pilot study [29], we estimate 60% will start insulin in the intervention group. A total of 224 participants from 74 general practices will provide sufficient power to detect a 40% change in the proportion that transition to insulin (power = 99.9%, assuming an intra-cluster correlation of 0.3). We will measure and compare the proportion of participants in each group that reach HbA1c target although our sample size is not powered to detect a significant difference in that.

The study will also have at least 80% power to detect an effect size of 0.5 of 1 SD for psychosocial scores, assuming an ICC of 0.05.

We do not anticipate a significant confounding of the results by the attention received by control group participants. In control group practices, GPs will be advised to undertake a clinical review of participating participants. In these practices, the PN will not receive training or support. In our intervention the PN once trained plays a critical enabling role in facilitating a simple in-practice system for insulin initiation. Without access to a trained PN and this system, background rates of insulin initiation by GPs in the control arm are likely to approximate those quoted above.

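### Baseline HbA1c is a prespecified covariate for continuous outcomes only; for the HbA1c-target outcomes it would enter only if an imbalance were seen, with no stated criterion

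*Protocol article*

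**What the plan says.** All references are to the protocol article.

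- **Outcome.** Under Outcomes, one of the two named secondary outcomes is "the proportion of participants who achieve HbA1c measurement of <7.0" per cent. Reaching an individualised HbA1c target is listed among the other measures of interest.
- **Binary model.** Under Statistical analysis: "Marginal logistic model using generalized estimating equations with robust standard errors will be used to compare binary outcomes between the two study arms". That sentence names no covariate.
- **Continuous model.** The next sentence uses mixed-effects linear regression to "compare the means between study arms for continuous outcomes, adjusting for baseline outcome measure".
- **Both models, on a natural reading.** "Stratification variables will be included as fixed effects", and the analysis is by intention to treat "with any imbalance of confounders between study groups adjusted for in the regression analysis". Neither statement is limited to one type of outcome.
- **Entry.** Under Participant identification and recruitment: "Patients are asked to have their HbA1c checked and are subsequently excluded if the result is <7.5" per cent.
- **Concealment.** Under Recruitment and randomization of practices, because "further patient recruitment often occurs over a period of months subsequent to randomization, full allocation concealment is not possible".
- **Power.** Under Power calculation and sample size, the groups will be compared on reaching HbA1c target, "although our sample size is not powered to detect a significant difference in that".

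**The concern.** Two models are specified side by side. One has its baseline covariate fixed in advance; the other does not. Reading the continuous-outcome phrase across to the binary model would not help with the below-7.0% outcome, because nobody can be below 7.0% at entry and a constant adjusts for nothing. The useful covariate is HbA1c itself on its continuous scale, which Table 1 shows is collected at baseline.

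Two things are at stake. The first is precision: someone who starts just above 7.5% has less far to fall than someone who starts at 10%, so baseline HbA1c should explain part of who reaches target. The second is protection against imbalance. Staff who know their practice's allocation continue to recruit, and the randomization is stratified by practice size, Community Health Center location and Collaboratives participation, not by HbA1c. A baseline difference between arms is therefore plausible, and whether it is adjusted for would be decided after the data have been seen.

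**Working it through.** **1. The article's only binary power figure.** For insulin start it states 20% against 60%, ICC 0.3 and power 99.9%. With 224/2 = 112 per arm and 3 per practice, the design effect is 1 + (3 - 1) x 0.3 = 1.6. That leaves 112/1.6 = 70 effective per arm, and the two-proportion power is 99.92%. The figure reproduces. No rate or power is stated for HbA1c below 7.0%, so the rest needs assumptions.

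**2. Inputs for HbA1c below 7.0%.**
- From the article: effect 0.5, SD about 1, ICC 0.05, 3 per practice, entry floor 7.5, and 74 practices with 10% lost (74 x 0.9 = 66.6, taken as 66, so 198 participants).
- Assumed: baseline mean 8.7 and SD 1 (skewed, floor 7.5); control mean at 12 months 8.0 or 8.4; slope of 12-month on baseline HbA1c 0.3 to 0.7.
- Model: exchangeable GEE logistic with robust standard errors, without and with continuous baseline HbA1c. Strata were not simulated. Each scenario had 500 runs, so the Monte Carlo error of one power figure is about sqrt(0.7 x 0.3/500) = 2 points.

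**3. Power when the arms are balanced in expectation, true effect 0.5.**

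| Control mean | Slope | Without baseline | With baseline | Gain (points) |
|---|---|---|---|---|
| 8.0 | 0.3 | 70.8% | 71.8% | 1.0 |
| 8.0 | 0.5 | 72.4% | 78.4% | 6.0 |
| 8.0 | 0.7 | 81.8% | 87.0% | 5.2 |
| 8.4 | 0.3 | 57.0% | 58.8% | 1.8 |
| 8.4 | 0.5 | 60.0% | 62.8% | 2.8 |
| 8.4 | 0.7 | 68.6% | 71.8% | 3.2 |

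**4. No true effect, intervention baseline 0.2 points higher, control mean 8.0.**

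| Slope | Mean log OR without | Mean log OR with | Rejection without | Rejection with |
|---|---|---|---|---|
| 0.3 | -0.147 (OR exp(-0.147) = 0.86) | -0.022 | 6.6% | 6.2% |
| 0.5 | -0.243 (OR exp(-0.243) = 0.78) | -0.021 | 9.4% | 4.6% |

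Here the bias runs against the intervention. An imbalance the other way would favour it.

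**5. What the imbalance clause would recover.** The clause has no criterion, so one has to be assumed: adjust only if the arms differ in baseline HbA1c at p < 0.05. Slope 0.5, control mean 8.0, 600 runs.

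| Scenario | Measure | Never adjusted | Triggered | Prespecified |
|---|---|---|---|---|
| Shift 0.2, effect 0.5 | Power | 52% | 63% | 73% |
| Shift 0.2, no effect | Mean log OR | -0.21 | -0.10 | 0.01 |
| Shift 0.3, no effect | Mean log OR | -0.32 | -0.10 | 0.01 |
| Shift 0.3, no effect | Rejection | 11% | 8% | 6% |
| No shift, effect 0.5 | Power | 71% | 72% | 78% |

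At a shift of 0.2 the trigger fired in 32% of runs. A hand check agrees: with 99 per arm and SD 1, 0.2/sqrt(2/99) = 1.41, and the chance of exceeding 1.96 is about 29%. The trigger leaves 0.10/0.32 = 31% to 0.10/0.21 = 48% of the bias, and at a shift of 0.2 it recovers (63 - 52)/(73 - 52) = 52% of the lost power. A looser threshold would fire more often and recover more.

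**The case against.** The strongest reply is that the same section already promises to check for imbalance in potential confounders and to adjust for any that is found, with no restriction to continuous outcomes. A reader who stops at the logistic sentence might infer that the binary outcomes are analysed with no adjustment for baseline HbA1c and that an imbalance carries over in full to the odds ratio. The article does not support that. The logistic sentence is not the whole model, since the strata are added later, and nothing excludes baseline HbA1c. The never-adjusted results in steps 4 and 5 are therefore a worst case, not a description of the plan. A fuller covariate list may also stand in an analysis plan that is not shown.

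It is also fair to say that the power gain is small, rests on assumed inputs, and concerns a secondary outcome that the article openly calls unpowered. A marginal logistic comparison with strata is a legitimate choice.

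What remains is narrower. The article does fix how baseline HbA1c could enter the binary model: after looking, by an unstated rule that does not name it. Such a rule leaves part of the bias in place, gives almost no precision when the arms look balanced (71% to 72%, against 78%), and leaves the covariate set open to choice once the data are known.

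**Conclusion.** The point holds as a minor one: for the HbA1c-target outcomes, adjustment for baseline HbA1c is contingent on observed imbalance where it could be fixed in advance. Under the assumptions in step 2, prespecifying it is worth about 1 to 6 points of power. With a 0.2-point imbalance, no true effect and slopes of 0.3 to 0.5, it removes a log odds ratio bias of about -0.15 to -0.24. That triggered adjustment removes this only in part was shown at slope 0.5 with a p < 0.05 trigger, and the share left depends on the criterion, which the article does not give.

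Limits:
- The primary analysis of HbA1c as a continuous variable is already baseline-adjusted and is unaffected.
- A reader might extend the point to a loss of power for insulin transfer. The article gives no support for that: it does not say how strongly baseline HbA1c predicts insulin start, and the stated power of 99.9% reproduces.
- The constant-baseline argument is exact for the below-7.0% outcome. The article does not list the individualised targets, so for that outcome some baseline values could differ; the case for the continuous covariate is the same.

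**What to change.** In Statistical analysis, state that the GEE logistic model for HbA1c below 7.0% and for the individualised target includes continuous baseline HbA1c together with the stratification variables, whatever imbalance is observed. Add that the arm odds ratio is then conditional on baseline HbA1c, so it is expected to lie further from 1 than the odds ratio without it even when the arms are balanced. A marginal contrast standardised over the baseline distribution may be reported alongside if a population-averaged figure is wanted.

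The cost is one covariate, one or two sentences and, if chosen, a standardisation step. No new data are needed, and Trial status says that data cleaning and analysis had not begun, so the choice could still be made in advance. If an unshown analysis plan already names this covariate, a cross-reference is enough.

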#### Economic evaluation

Medicare Benefits Scheme (MBS) and Pharmaceutical Benefits Scheme (PBS) data between 1 October 2011 and 1 February 2016 will be obtained to examine health services utilization prior, during, and after study period. The submission was approved by Medicare Australia in October 2012 (reference 2012/CO11645). An additional Medicare consent will be sought from each participant using the Medicare Australia consent form. Data extraction will occur in May 2016. Furthermore, a submission will be made to the Victorian Department of Health to obtain data linkage on the Victorian Admitted Episodes Datasets (VAED) and the Victorian Emergency Minimum Datasets (VEMD).

A within-trial Cost-utility analysis (CUA) will be undertaken from the perspective of the healthcare system. The primary effectiveness outcome, quality-adjusted life years, will be calculated from the AQOL-8D. We will calculate the cost of the Stepping Up Program, distinguishing implementation from establishment and trial-specific costs. The mean per participant cost of healthcare will be estimated for both intervention and control clients, based on the audit of clinical records, participant questionnaire and data linkage, as described above. The intervention group will incur the additional costs of the Stepping Up Program. One-way sensitivity analyses will be undertaken to identify the key cost and outcome drivers. A stratified analysis will be used for subgroups where the Stepping Up Program may have any greater or lesser effectiveness, defined *a priori*.

### Trial status

Baseline data collection is ongoing and we anticipate will be completed in February 214. Follow up data collection should be completed by mid-2016. Data cleaning or analysis has not yet begun.

## Discussion

The Stepping Up trial has been designed as a translational study, testing the implementation of a known efficacious intervention (insulin for treating hyperglycemia) into real world practice in primary care. One of the study’s key strength is that it is a pragmatic trial examining the real world effectiveness of reorienting care systems and the use of existing human healthcare resources to address a persistent clinical problem. It has important potential implications for people with T2D, healthcare professionals, and funders of healthcare though making better use of scarce healthcare resources, improving timely access to therapy that can improve disease outcomes.

If successful, it will inform chronic disease and diabetes routine care, policy, and funding. PNs are the fastest growing section of the primary care workforce. Almost 60% of practices employ at least one PN [28], and as core members of general practice teams, they are increasingly important in addressing the epidemic of chronic disease [45], attracting significant government interest and investment. PNs potentially have a much broader and more autonomous role than traditional clinic nurses, yet overall have had little formal training in such a role [46]. Prior research has shown that people with T2D are receptive to enhanced PN involvement in their care [47], and that PNs are keen to enhance their role within diabetes care. PNs are often able to offer the time, support, and care required to respond to the psychosocial and emotional needs of people with T2D [48]. However, local practice context and culture issues need to be addressed [49]. The Stepping Up intervention supports the GP/PN team by clarifying roles, work relationships and responsibilities.

The intervention has the potential to demonstrate significant improvements in biochemical and clinical markers known to be associated with improved outcomes in people with T2D. The study will also provide important evidence about the impact on psychosocial outcomes for people with T2D participating in the model of care and for those commencing insulin therapy in primary care.

A cost analysis of the Stepping Up program and its impact on disease progression and downstream costs within in Australia will have local relevance. This study will investigate how the costs of diabetes care are affected by better integration of PN, GP, endocrinologist and CDE-RN in the general practice setting, based on real-world implementation of the stepping Up program taking into account the support required to initiate and sustain change in practice. The expectation is of downstream cost savings through reduction of future diabetes-related complications.

Our proposed study also directly contributes to building a research culture in Australian general practice. The practices (GPs and PNs) involved in Stepping Up will be supporting part of a state wide practice-based research network to enhance primary care research capacity in Australia.

## Abbreviations

T2D: Type 2 diabetes; RA: Research assistant; SET: Screening eligibility tool; PLS: Plain language statement; BDQ: Brief demographic questionnaire; BG: Blood glucose; BGM: Blood glucose meter; GP: General practitioner; PN: Practice nurse; CDE-RN: Credentialed diabetes educator- registered nurse.
